## Abstract

**Background:**

Diabetes is the western world’s leading cause of end-stage renal disease. Glucose-dependent, oxidative stress is linked to the development of renal inflammation and sclerosis, which, in animal models of diabetes, can be prevented by anti-oxidative treatment. Patients of non-Caucasian heritage have low activity of the selenoprotein, antioxidant enzyme, glutathione peroxidase (GPx) and its co-factor vitamin E, which may be linked to their increased propensity to developing end-stage renal disease.

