**Research design and methods:**

We have designed a double-blind, randomized, placebo controlled study with selenium and/or vitamin E versus placebo as the interventions for patients with type 2 diabetes and chronic kidney disease (CKD) stages 1–3. A 2 × 2 factorial design will allow a balanced representation of the heritage groups exposed to each intervention. The primary biochemical outcome is change in GPx activity, and clinical outcome measure is the actual, rate of—and/or percentage change in estimated glomerular filtration rate (eGFR) from baseline. Analysis will be with a marginal model for longitudinal data using Generalized Estimating Equations corrected for measures of baseline serum antioxidant enzyme activities (GPx, superoxide dismutase and catalase), micronutrient levels (vitamins E and C), measures of inflammation (interleukin 6, c-reactive protein and monocyte chemoattractant protein-1) and markers of oxidative damage (plasma 8-isoprostaglandin F2α and urinary 8-hydroxydeoxyguanosine).

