Markers of oxidative stress are increased in the circulation and renal tissue of patients with diabetes compared with control patients without diabetes [8, 9]. Patients of African origin have been found to have higher circulating levels of lipid peroxide, lower concentrations of vitamin E and faster rates of decline in renal function compared with those of Caucasian heritage [10, 11]. Relatively low levels of serum selenium have been reported in people of Asian origin [12]. Selenium is a co-factor for the antioxidant enzyme GPx, and low levels are associated with an upregulation of inflammatory chemokines. Selenium supplementation attenuates the inflammatory response and in systemic inflammatory disease states may improve clinical outcomes [13, 14].

The activity of GPx in plasma is largely derived from renal tubular epithelium and is reduced in the presence of renal disease [15, 16]. It is unclear whether the level of activity of GPx contributes to the susceptibility to progressive renal disease. In this study, we will compare the effect over time of antioxidant therapy with vitamin E and/or selenium in patients with type 2 diabetes and early CKD, on measures of systemic inflammation, antioxidant enzyme activity and changes in eGFR.

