### Statistical analysis

In this 2 × 2 factorial design, selenium and vitamin E are considered the two factors. The data will be analyzed with a linear mixed model for longitudinal data [24]. In the model, eGFR is the dependent variable and time is an independent variable; the model will also contain as independent variables a dummy variable for each of the two factors, a term for the two-way interaction between the two factors, and continuous covariates for various measures of oxidative stress and inflammation at baseline. The model allows for the correlation between repeated measures on the same individual, but assumes that there is independence from one subject to the next. The correlation within measurements on a given subject will be modeled using compound symmetry as well as an autoregressive correlation structure. Whichever structure gives the best fitting model to the data will be used.

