## Results

The primary hypothesis of interest in this study is whether there is an interaction between the selenium and Vitamin E supplements. If interaction is present, then the effect of each supplement will have to be estimated separately in the presence and absence of the other supplement. If no interaction is present, then it will be possible to estimate the main effects of selenium and Vitamin E separately without having to take the other supplement into consideration.

The effect sizes are conservative and will be based on the estimated changes from baseline to 1 year [25]. A study population of 150 will have 85 % power to detect an ES of 1.0 SD, and a population of 200 will have 83 % power to detect an ES of 0.85 SD at a two-sided alpha level of 5 % [26].

The two heritage groups will have their eGFR slopes compared over time and considered as either, (a) Caucasian and non-Caucasian, or (b) High and Low levels of oxidative stress/inflammation, with the oxidative stress and inflammation markers dichotomized at their median value. The power will not be heavily dependent on any of the assumptions; regardless of the true value of the underlying correlation among observations with subjects, of the correlation structure, of the attrition rate, or of the number of repeated measurements.

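### The High/Low oxidative-stress comparison of eGFR slopes is not separated from heritage, so as stated it would carry part of any heritage difference in slope

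*Protocol article*

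**What the plan says.** All references are to the protocol article.

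- **Results.** The slopes of the two heritage groups will be compared over time, "considered as either, (a) Caucasian and non-Caucasian, or (b) High and Low levels of oxidative stress/inflammation". The second grouping uses a median split of each marker. No comparison is described that holds heritage and marker level together.
- **Statistical analysis.** The model for eGFR contains time and, for treatment, "a dummy variable for each of the two factors, a term for the two-way interaction between the two factors". The only further terms named are baseline measures of oxidative stress and inflammation, entered as continuous covariates. Heritage is not listed, and no marker is multiplied by time.
- **Abstract, Research design and methods.** The analysis is to be "corrected for measures of baseline serum antioxidant enzyme activities", together with vitamins, inflammatory markers and markers of oxidative damage. Heritage is not in that list either.
- **Abstract, Background.** Patients of non-Caucasian heritage are said to have low GPx activity and low vitamin E, "which may be linked to their increased propensity to developing end-stage renal disease".
- **Background and Discussion.** Patients of African origin are described as having more lipid peroxide, less vitamin E and faster renal decline. The investigators report having themselves found lower GPx activity in this group.
- **Aims.** The Abstract (Expected results) promises to assess how GPx, oxidative stress, inflammation and eGFR are related. The Discussion promises information on whether early CKD progression depends on oxidative stress. The primary hypothesis is a different one: "The primary hypothesis of interest in this study is whether there is an interaction between the selenium and Vitamin E supplements".

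**The concern.** If heritage and marker level are correlated, as the article's rationale supposes, the High stratum will contain more non-Caucasian patients than the Low stratum. Any difference in slope that belongs to heritage for other reasons then appears in the High/Low comparison as well. Balancing heritage across the treatment arms does not help, because it does not balance heritage across the marker strata.

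The main model as listed does not repair this. A baseline marker entered without a time interaction shifts the level of eGFR, not its slope. Even if a heritage-by-time term were added, the slope comparison would remain essentially unadjusted for marker-related differences in slope.

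At stake is the interpretation of a secondary result. A High/Low difference could be reported as an association with oxidative stress when part of it is heritage. That comparison is the stated slope analysis closest to the aim of relating oxidative stress to progression.

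**Working it through.** **1. The plan's own figures.** The article states no figure for the slope comparison by heritage or by marker. Its power statement is 85% for N = 150 at 1.0 SD and 83% for N = 200 at 0.85 SD, two-sided 5%. I checked whether this refers to the comparison at issue. For a 2 × 2 interaction contrast, SE = SD × √(4/n) with n = N/4 per cell:

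- N = 150: √(4/37.5) = 0.327; 1.0/0.327 = 3.06; noncentral t with 146 df gives 0.860.
- N = 200: √(4/50) = 0.283; 0.85/0.283 = 3.01; noncentral t with 196 df gives 0.849.

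Both lie within two percentage points of the stated values. The power statement therefore fits the selenium by vitamin E interaction and says nothing about the slope comparison here.

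**2. How much of the heritage difference leaks into High/Low.** Assumptions: heritage groups of equal size (the article intends balanced representation but gives no shares); marker normally distributed with equal variance; means d SD apart; split at the pooled median; additive effects on slope.

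The pooled median lies midway between the two means, so the share of non-Caucasian patients is Φ(d/2) in the High stratum and 1 − Φ(d/2) in the Low stratum. Let α be the heritage slope difference that does not run through the marker. If the marker has no effect of its own, α is the whole heritage difference and

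High − Low = α × [2Φ(d/2) − 1].

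| d (SD, assumed) | 2Φ(d/2) − 1 | share of heritage difference shown |
|---|---|---|
| 0.3 | 0.119 | 12% |
| 0.5 | 0.197 | 20% |
| 0.8 | 0.311 | 31% |
| 1.0 | 0.383 | 38% |

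If the marker does affect slope, the same share of α is added to the marker's own contribution, and the comparison as stated cannot separate the two.

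**3. Whether a joint model is affordable.** Assumptions: N = 200, heritage 100/100, 80% power, two-sided 5%, slopes in SD units. With correlation r between heritage and marker, the minimum detectable heritage difference is

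(1.960 + 0.842) × √[(4/200) / (1 − r²)].

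| r (assumed) | 1/(1 − r²) | detectable difference (SD) |
|---|---|---|
| 0 | 1.000 | 0.396 |
| 0.3 | 1.099 | 0.415 |
| 0.5 | 1.333 | 0.457 |
| 0.7 | 1.961 | 0.555 |

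For r of 0.3 to 0.5 the interval widens by √1.099 − 1 = 5% to √1.333 − 1 = 15%. To link this with step 2: for a continuous marker with group means d SD apart, 1/(1 − r²) = 1 + d²/4. That is 1.0225 at d = 0.3 and 1.25 at d = 1.0, or intervals 1% to 12% wider. These figures are for one marker; several correlated markers would cost more.

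**The case against.** The strongest reply is that the trial never sets itself the task of explaining a heritage difference. Its stated comparison is of treatment ("we will compare the effect over time of antioxidant therapy with vitamin E and/or selenium"), its primary hypothesis is the interaction, and the link between heritage and antioxidant status is offered as motivation. The slope sentence is one line on a non-randomised comparison in a condensed article, placed next to the power statement. It names two groupings and does not exclude covariates. The marker gaps used above are assumed, and the shares apply to a heritage difference of unknown size, so no bias in eGFR units follows. A before-and-after change in a coefficient is also only observational; the Discussion itself says that hypertension and proteinuria account for some of the difference in progression.

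Most of this stands, and it limits the point. A reader might infer that the trial cannot tell whether oxidative stress explains the heritage difference. The documents do not support that: heritage and the baseline markers are to be recorded, a joint model is feasible at N = 200, and explaining the difference is not a stated objective. A reader might also infer that adjusting for baseline GPx and vitamin E removes the hypothesised pathway. That does not follow either. The article does not say that the heritage contrast comes from the adjusted model, and covariates without a time interaction would not remove a pathway that acts on slope.

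What the reply does not meet is narrower. The article does more than stay silent. It specifies the slope comparison as one grouping or the other, and its own premise makes the two groupings overlap. Relating oxidative stress to progression is a stated aim whether or not heritage is named in it.

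**Conclusion.** The point holds as a weakness in a stated secondary analysis. The High/Low slope comparison, as described, is confounded by heritage. Its size is about 12% to 38% of the heritage slope difference, given equal heritage groups, normal markers of equal variance, a gap of 0.3 to 1.0 SD and no marker effect. The article supplies neither the gap nor the heritage slope difference, so the absolute bias is unknown. The unadjusted heritage comparison remains a legitimate description of the total difference; it does not show how far that difference is accompanied by differences in the markers. The primary selenium by vitamin E question is unaffected.

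**What to change.** In the Results section, replace the either/or grouping by one longitudinal model that:

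- keeps the treatment terms of the Statistical analysis section;
- includes heritage and heritage-by-time;
- includes marker and marker-by-time for a short prespecified set of markers, kept continuous as in that section and not split at the median.

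Report the association of each marker with slope adjusted for heritage. Report the heritage slope difference from the model without the marker terms and from the model with them, with an interval for each and a bootstrap interval for the change. Label these results as secondary and observational, not as proof of mediation.

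The cost is a change of wording and one further model fit on data already to be collected. The adjusted heritage interval would be about 5% to 15% wider for a heritage–marker correlation of 0.3 to 0.5, and more if several correlated markers enter together, which is a reason to keep the set short.

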## Subjects

We plan to recruit a total of 200 adult patients with type 2 diabetes of white, Caucasian and non-Caucasian (African, Caribbean or Indo-Asian) heritage from general practices in South West London, UK. An equal number of eligible patients will be randomized to receive, either, active selenium (200 μg once daily) or its placebo and/or vitamin E (400 IU once daily) or its placebo in a 2 × 2 factorial design (Fig. 1). Treatment allocation will be according to a computer generated code for each group to which the patients and researchers will be blinded.

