The total triglyceride contents of plasma and lipoprotein fractions will be measured by an enzymatic colorimetric method (Triglycerides GPO-PAP; Sigma Diagnostics). In brief, an aliquot of plasma sample (10 µL) will be mixed with 900 µL of a reagent containing a lipase to deacylate triglycerides and liberate glycerol. This will then be phosphorylated to glucose-1-phosphate and the product oxidised by glucose phosphate oxidase with the formation of hydrogen peroxide (H_2_O_2_). The H_2_O_2_ formed will then be coupled with horseradish peroxidase to give a pink product, the absorption of which will be measured in a spectrophotometer at 500 nm.

Vitamin C as total ascorbate (sum of oxidised and reduced ascorbate) will be measured by enzymatic oxidation of reduced ascorbic acid to dehydroascorbate acid followed by reaction of the dehydroascorbate formed with o-phenylenediamine to give a fluorescent product [21]. Two hundred and fifty microliters of plasma will be mixed with 250 μL metaphosphoric acid (20 % w/v) and centrifuged at 13 000×*g* for 5 min. 50 μL of the supernatants will be combined with 900 μL of sodium acetate buffer (2 mol/L, pH 6.2) and ascorbate oxidase (10 μL of 1 U/1 μL in sodium acetate buffer). o-1, 2-diphenylenediamine (20 μL, 1 mg/mL) is then added and the samples are incubated for 30 min at room temperature in the dark. Finally, the fluorescent signals will be read in spectrofluorometer at excitation at emission wavelengths of 350 and 430 nm, respectively. The inter- and intra-assay c.v. are 1 and 2.5 %, respectively.

Selenium will be measured in serum as described by Rayman et al. [22]. The analysis will be carried out at the SAS Trace Element Unit, Southampton General Hospital using dynamic reaction cell-inductively coupled plasma MS on an Elan 6100 DRC plus (SCIEX Perkin-Elmer).

Oxidative stress will be assessed by measuring (1) plasma and urinary free 8-iso prostaglandin F2α using an ELISA kit (Cayman Chemical, Ann Arbor, MI, USA) and (2) urinary 8-hydroxydeoxyguanosine (8-OHdG) as a marker of deoxyribonucleic acid damage using an ELISA kit according to the manufacturer’s instructions (Cambridge Biosciences Ltd, Cambridge, UK).

Inflammation will be assessed by measuring c-reactive protein, interleukin-6 and monocyte chemoattractant protein-1 by ELISA kits according to the manufacturer’s instructions (ThermoFisher Scientific, Paisley, UK).

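### The only stated analysis of marker level against eGFR slope uses a median split, and it is worded as a second form of the heritage groups

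*Protocol article*

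**What the plan says.** The rule stands in the Results section of the protocol article. It first names what is grouped: "The two heritage groups will have their eGFR slopes compared over time and considered as either, (a) Caucasian and non-Caucasian, or (b) High and Low" (the last two words refer to marker level). For this second option the cut is then fixed at the sample median of each marker: "with the oxidative stress and inflammation markers dichotomized at their median value". No reason is given for the split.

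The Statistical analysis section describes a longitudinal eGFR model containing time, one dummy variable for each supplement, their interaction, and "continuous covariates for various measures of oxidative stress and inflammation at baseline". It lists no product of a marker with time.

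The Biochemical assessments section names three inflammation markers: "Inflammation will be assessed by measuring c-reactive protein, interleukin-6 and monocyte chemoattractant protein-1". For oxidative stress it names an isoprostane, measured in plasma and urine, and urinary 8-hydroxydeoxyguanosine.

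The Abstract (Expected results) gives the relation between oxidative stress, inflammation and eGFR as something the study will assess. The last paragraph of the Discussion promises information on whether progression of early CKD is tied to oxidative stress.

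**The concern.** There are two faults in one sentence.

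- **The split.** Cutting a continuous marker at the sample median treats patients just either side of the cut as opposites and everyone on one side as alike. The cut point also depends on who happened to be recruited. Where the marker has a graded relation with slope, this discards information.
- **The merging.** High and low marker level is presented as a way of forming the two heritage groups. Whether heritage groups differ in slope and whether marker level predicts slope are separate questions. A single either/or grouping states neither clearly.

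At stake is the power to answer a question that the article names among its aims, and a clear definition of the heritage comparison.

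**Working it through.** **1. The plan's own figures.** The article gives power for two sizes at two-sided 5%: "A study population of 150 will have 85 % power to detect an ES of 1.0 SD", and 83% for 200 patients at 0.85 SD. It gives no power for the marker-slope comparison and no figure for the split. Taking the primary hypothesis, the supplement interaction, with four equal cells, SE = 4·SD/√N:

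- N = 150: SE = 4/√150 = 0.327 SD; 1.0/0.327 = 3.06; power = Φ(3.06 − 1.96) = 86.5% (noncentral t, 146 df: 86.0%).
- N = 200: SE = 4/√200 = 0.283 SD; 0.85/0.283 = 3.01; power = Φ(3.01 − 1.96) = 85.2% (noncentral t, 196 df: 84.9%).

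The t-based values lie within 2 points of the stated 85% and 83%. A t-test between two groups of N/8 each also comes close (84.6% and 83.8%). Two halves of the sample, which is what a High/Low split would give, yield more than 99.9%. The stated power therefore does not appear to describe the High/Low comparison.

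**2. Is the split the only marker-slope analysis?** In the Statistical analysis section a marker enters as a baseline covariate without a time product. Such a term shifts the level of eGFR; it does not let the rate of change vary with the marker. The Results section is the only place where slopes are compared by marker level.

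**3. Information kept by a median split.** For a linear relation, the share kept is the squared correlation between the marker X and its indicator of lying above the median. For a standard normal X:

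- covariance = φ(0) = 0.399; SD of the indicator = 0.5
- correlation = 0.399/0.5 = 0.798
- share kept = 0.798² = 2/π = 0.637; loss = 36.3% (a simulated marker gave 0.636 kept)

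For this comparison alone, 200 patients carry the information of 200 × 0.637 = 127, and 150 that of 95. Matching the continuous analysis of 200 would take 200 × π/2 = 314.

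**4. Effect on power.** Power after the split = Φ[(1.96 + z)·√(2/π) − 1.96], where z is the normal quantile of the power with the marker continuous. The starting powers are illustrative.

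| Continuous | Calculation | After split |
|---|---|---|
| 80% | Φ(2.80 × 0.798 − 1.96) = Φ(0.28) | 61% |
| 90% | Φ(3.24 × 0.798 − 1.96) = Φ(0.63) | 73% |

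A simulation with N = 200 and a marker-slope correlation of 0.20 (an assumed value) gave 82% continuous and 61% split.

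**5. Range.** The article states neither the marker distributions nor the form of the relation, so the loss is shown under several assumptions.

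| Assumed marker, effect linear on the scale named | Kept | Lost |
|---|---|---|
| Uniform | 0.75 | 25% |
| Normal, or log-normal with the effect on the log scale | 0.64 | 36% |
| t with 5 df | 0.54 | 46% |
| Log-normal, raw-scale effect, log-SD 0.3 | 0.59 | 41% |
| Log-normal, raw-scale effect, log-SD 1.0 | 0.27 | 73% |

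**The case against.** The strongest reply is that this is one loosely drafted sentence about a secondary comparison in an article that condenses a fuller plan. The two sections describe different analyses, so continuous markers in one and split markers in the other is not a contradiction. The efficiency figure also rests on assumptions that the article does not make. All of that stands, and it limits the point. It does not remove it: the article fixes the split as a rule, and the continuous model as listed does not address slope. How several markers would yield one High/Low status may be left to the full plan and is not held against the article.

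A reader might infer four stronger things that the documents do not support.

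- **That the stated power is wrong, or that the trial in effect loses 73 of its 200 patients.** The 85% and 83% fit the interaction contrast, which does not use the split. The loss of 200 − 127 = 73 applies to the marker-slope comparison only.
- **That the split leaves residual confounding in the heritage comparison.** The split marker forms its own grouping and is never used to adjust Caucasian versus non-Caucasian. Where markers serve as adjustment variables they are continuous. The Background also presents oxidative stress as a possible step between heritage and renal disease, so calling it a confounder would be doubtful.
- **That the grouping will be chosen after the results are seen.** The wording allows that reading, but it equally allows two planned comparisons, both to be reported.
- **That about a third of the information is lost as a matter of fact.** That figure is conditional, as the range shows.

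**Conclusion.** The point holds for the secondary marker-slope comparison. A median split is the only stated way of examining whether marker level relates to eGFR slope, and the sentence merges that question with heritage. If a marker is roughly normal, raw or logged, and linearly related to slope, the loss is 36% of the information, enough to take 80% power to about 61%. Under the other distributions tried the loss runs from about 25% to 73%. The assumed distribution, the linear relation and the starting power are not in the document. The primary selenium by vitamin E interaction and its stated power are untouched. This should be changed, but it does not threaten the main analysis.

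**What to change.** Replace the sentence in the Results section with two separate statements.

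1. **Heritage.** Compare eGFR slopes between Caucasian and non-Caucasian patients through a heritage-by-time term. Use no other definition of the heritage groups.
2. **Markers.** As a separate secondary comparison, relate each baseline marker to eGFR slope as a continuous variable, logged if skewed, with a marker-by-time term and a simple linearity check. Use median groups for description and figures only.

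This brings the marker analysis into line with the continuous form already used in the Statistical analysis section. Further products of heritage with treatment and time are not needed to cure the fault. The cost is wording: no extra patients, visits or assays. The small downside is a linearity assumption that has to be checked.

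### The power statement is wrong to call the design robust to attrition: the stated 83–85% for the primary interaction needs about 95–100% of patients analysed, and the effect sizes are called conservative without support

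*Protocol article*

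**What the plan says.** All of the power material is in the protocol article, Results section, apart from the recruitment target and allocation in Subjects.

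- Primary question: "The primary hypothesis of interest in this study is whether there is an interaction between the selenium and Vitamin E supplements".
- Basis of the effect sizes: "The effect sizes are conservative and will be based on the estimated changes from baseline to 1 year".
- Power: for 150 patients it is put at 85% for an effect of 1.0 SD. For the planned size the article states that "a population of 200 will have 83 % power to detect an ES of 0.85 SD at a two-sided alpha level of 5" percent.
- Robustness: "The power will not be heavily dependent on any of the assumptions". Among the things said not to matter are the within-subject correlation and the effects "of the correlation structure, of the attrition rate, or of the number of repeated measurements".
- Recruitment (Subjects): "We plan to recruit a total of 200 adult patients with type 2 diabetes". Allocation is equal over the four cells of the factorial: "An equal number of eligible patients will be randomized to receive" each combination.

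The article gives no SD in eGFR units, expected eGFR difference, loss rate or correlation value. It does not say which contrast the effect size refers to.

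**The concern.** The robustness sentence is a positive claim about the design, not a detail that a condensed article has left out. Power for any contrast depends on how many patients supply data. When an effect is fixed in outcome units, power also depends on the within-patient correlation and on the visits used.

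Two things are at stake. First, a reader told that attrition hardly matters has little reason to plan for it in a trial that follows patients to 24 months. Second, the Results section uses the interaction result to decide whether each supplement's main effect may be estimated without regard to the other. If the interaction test is described as well powered and robust when it detects only large interactions, a non-significant result will too easily be read as showing that no interaction exists.

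**Working it through.** **Inputs.** Contrast: the interaction (Results). Four equal cells of N/4 (Subjects). Two-sided alpha 5%; effect sizes of 1.0 SD at N = 150 and 0.85 SD at N = 200 (Results). One change value per patient, because the effect sizes rest on change from baseline to 1 year (Results). Loss rates are assumed, because none is stated.

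**Reproducing the stated power.** The interaction is a difference of differences between four cell means, so

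SE = SD × √(4 / (N/4)) = 4 × SD / √N.

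- N = 150: SE = 4/√150 = 0.3266 SD; 1.0/0.3266 = 3.062. Noncentral t with 146 df gives 86.0% (stated 85%).
- N = 200: SE = 4/√200 = 0.2828 SD; 0.85/0.2828 = 3.005. Noncentral t with 196 df gives 84.9% (stated 83%).

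Both are within 2 points. The stated values are met exactly at about 146 of 150 analysed (3% loss) and 190 of 200 (5% loss).

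Other contrasts on the whole sample do not fit. A main effect gives over 99.9% at both sizes, and one cell against another gives 99.1% and 98.9%. A comparison of two cells inside one of two equal heritage groups does fit: 85.1% with 19 v 19 and 83.8% with 25 v 25. The article does not describe that contrast as primary.

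**Effect of loss** (N = 200, 0.85 SD, lost patients contribute nothing):

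| Loss | Analysed | SE (SD units) | 0.85/SE | Power |
|---|---|---|---|---|
| 0% | 200 | 0.2828 | 3.005 | 84.9% |
| 5% | 190 | 0.2902 | 2.929 | 83.0% |
| 10% | 180 | 0.2981 | 2.851 | 80.9% |
| 15% | 170 | 0.3068 | 2.771 | 78.7% |
| 20% | 160 | 0.3162 | 2.688 | 76.2% |
| 30% | 140 | 0.3381 | 2.514 | 70.4% |

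For N = 150 and 1.0 SD, power is 82.2%, 77.5% and 71.8% at 10%, 20% and 30% loss. The heritage-stratum cell pair behaves the same way. With SE = SD × √(2/n), starting from 25 per cell and 0.85 SD, 20% loss leaves 20 v 20 and 74.5% power.

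**Size of the effect.** At N = 200 with 80% power (normal approximation, 1.960 + 0.842 = 2.802):

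- Main effect: 2/√200 × 2.802 = 0.396 SD.
- Interaction: 4/√200 × 2.802 = 0.792 SD.

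The assumed 0.85 SD is 0.85/0.396 = 2.1 times the detectable main effect. With no loss, interaction power is 42% for 0.5 SD and 18% for 0.3 SD.

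**Correlation, structure and visits** (illustrative; N = 200, no loss, normal approximation, effect fixed in SDs of a single eGFR value):

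- Change score, SD of change = SD × √(2(1 − ρ)), effect 0.85 SD: 71.9% at ρ = 0.3, 85.2% at 0.5, 97.3% at 0.7.
- Time-averaged effect of 0.85 SD, compound symmetry, ρ = 0.5: 85.2% with one visit, 96.7% with four, 97.6% with six.
- Slope interaction of 0.5 SD per year, all seven time points, ρ = 0.5: 99.7% under compound symmetry, 78.7% under a first-order autoregressive structure (correlation by visit order).

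These show that the dependence exists. Its size in this trial cannot be fixed without a definition of the effect size.

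**The case against.** Several points on the other side have force.

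- **The text says not heavily dependent.** It does not claim complete independence, and it does not promise power whatever happens. That stands. Even so, a fall from 85% to 76% at 20% loss and 70% at 30% is material.
- **The stated power tolerates some loss.** A reader might infer that 83–85% holds only with complete retention. It does not: the stated figures lie 1 to 2 points below the no-loss values, and at 10% loss the larger design still has 81%.
- **The mixed model uses partial data.** This stands as a qualification, since the table counts lost patients as contributing nothing. With a time-averaged 0.85 SD interaction over six visits (compound symmetry, ρ = 0.5), power is about 97–98% with no loss and 94% with 20% wholly lost. But the article gives neither that effect definition nor that correlation, and it bases its effect sizes on the 1-year change.
- **The sentence follows the heritage-group comparison.** A two-group comparison of 0.85 SD has over 99.9% power at 200 and 98.8% with half the patients lost. That is indeed robust, but it does not match the stated 83–85%, which the sentence appears to qualify.
- **Conservative may be justified elsewhere.** A reader might infer that the word is false. The article does not allow that conclusion: it gives no SD or expected effect, it rests on a cited source, and the word may refer to using a 1-year change in a 24-month trial. It is unsupported, not disproved.
- **Correlation may already be absorbed.** If the effect size is in SDs of the 1-year change, the correlation is inside that SD. This stands, so the correlation examples carry no firm number for this trial.
- **150 may be the expected number of completers out of 200.** The article does not say so. If it were, the power to quote would be 85% for 1.0 SD, and the 83% for 0.85 SD at 200 would not be what the trial expects to have.

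**Conclusion.** The claim that power is not heavily dependent on attrition, correlation, structure or number of measurements is wrong for the primary interaction. The stated figures correspond to about 95–100% of recruited patients being analysed. At N = 200 and 0.85 SD, power falls below 80% between 10% and 15% complete loss and reaches about 76% at 20% and 70% at 30%.

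This rests on four assumptions: the effect size refers to the interaction (inferred, because it reproduces both figures); there is one change value per patient; lost patients contribute nothing; and the loss rates are illustrative. Partial data would reduce the drop. Dependence on correlation and visits is real when the effect is fixed in eGFR units, but it cannot be quantified from the article.

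The description of the effect sizes as conservative is unsupported. The trial is powered for a large interaction only, which limits what a non-significant interaction can show. The sample size itself is not shown to be wrong.

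**What to change.** 1. Delete the robustness sentence, or replace it with power over an explicit range of loss at N = 200. For a 0.85 SD interaction with lost patients contributing nothing, this is 85%, 81%, 76% and 70% at 0%, 10%, 20% and 30%.
2. Drop the word conservative, or justify it with the expected eGFR effect and its SD.
3. Name the contrast to which the effect size refers and the SD it is measured in (a single eGFR value, 1-year change or slope). Give the detectable effects in mL/min/1.73 m². If correlation or visit number enters under that definition, show power over a range of those too.
4. State that a non-significant interaction will not be taken as evidence that no interaction exists.

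Keep recruitment at 200. These are changes of text only; the cost is a stated power that looks less favourable.
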